## Safety

Since this study is observational, there are no direct risks associated with participation. All cervical ripening methods were used in accordance with the French marketing authorizations.

## Statistical consideration

### Sample size estimation

The maternity unit delivers approximately 2,600 infants a year. We consider that 20% of women will meet the criteria for inclusion in the maternity unit, thus around 40 per month. An inclusion period of 20 months should make it possible to recruit 800 women, if we assume a participation rate of at least 95% and a 40% drop-out rate at 3 months.

### Statistical analysis

Continuous data will be described by their means ± standard deviations and compared by t tests (or Mann-Whitney tests when appropriate), and categorical data will be described by percentages and compared by χ^2^ tests (or Fisher’s exact tests when appropriate). Maternal and perinatal outcomes will be compared according to cervical ripening method. For the analysis of dissatisfaction in immediate postpartum period, a score < 5 will be considered as a negative result and defined as “dissatisfied”. Maternal QOL at 3 months, assessed by use of EQ-5D-5L scores estimated with the most up-to-date preference-based value set [11,12], will be summarized in each group using mean ± standard deviations and compared between groups using mean differences (99% confidence index). In the five domains of QOL, we will dichotomise into women reporting problems versus reporting no problems and will calculate the outcomes for the different groups. The associations between women’s dissatisfaction at immediate postpartum period and poor QOL at 3 months post-delivery and the characteristics of their pregnancy, cervical ripening methods, labor, and delivery will be then assessed with a multivariate logistic regression model. All analyses were carried out using R software (version 4.0.2). P values <0.05 were considered to be statistically significant.

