### Target population

All consecutive pregnant women who required device for cervical ripening before IOL with a live fetus, an unfavorable Bishop score (<6) and a normal pre-induction cardiotocograph (CTG) in a tertiary care hospital with more than 2,600 annual deliveries are consecutively included. The choice of the method of cervical ripening (DBC, vaginal dinoprostone insert or oral misoprostol) is left to the free discretion of the obstetrician responsible for the woman at the beginning of IOL.

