### Trial design and follow-up

Participant registration for the study will run from January 9, 2020 to August 9, 2021, and women participation will run from January 9, 2020 to November 9, 2021. All women will require device for cervical ripening for IOL with an unfavorable cervix (Bishop score <6) with a live fetus at term whatever the indication for IOL. The choice of the cervical ripening method (DBC, vaginal dinoprostone insert or oral misoprostol) is left to the free discretion of the obstetrician responsible for the woman at the beginning of IOL, but in accordance with the institutional local guidelines for cervical ripening. DBC (Cervical Ripener Balloon®, Cook OB/GYN, Spencer, IN, USA) and vaginal dinoprostone insert (Propess®, Ferring, Saint-Prex, Switzerland) with 10 mg slow-release dinoprostone) are approved for use up to 24 hours. Oral misoprostol (Angusta®, Azanta, Valby, Denmark) may be used for more than 24 hours (20μg per day). If labor does not ensue or the Bishop score is still unfavorable (score<6) after 24 hours, there is no consensus and repeating the vaginal dinoprostone insert or oral misoprostol or switching to another method are options to the free discretion of the treating physician. The choice of the maximum duration of cervical ripening permitted before starting oxytocin if membranes are not accessible is also left to the free discretion of the treating physician with a maximum of 3 days in our obstetric team. Once Bishop’s score is ≥ 6, further management with oxytocin induction is recommended in our team.

Maternal sociodemographic characteristics, information regarding pregnancy follow-up, cervical ripening, standard perinatal outcomes, immediate women’s experience and satisfaction and long-term health-related QOL will be collected by one obstetrician (GD) from a prospectively maintained database of women who will be included throughout the study period.

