Nevertheless, the study presents certain limitations. First, the choice of the method of cervical ripening (DBC, vaginal dinoprostone insert or oral misoprostol) will be left to the free discretion of the obstetrician responsible for the woman at the beginning of IOL. That can introduce selection bias if participants regarding cervical ripening methods differ in important ways other than outcome. Second, our research will be not blinded, it is not possible to blind women and medical staff due to the nature of the intervention (e.g., CRB vs. vaginal dinoprostone insert vs. oral misoprostol), that may affect the physician’s strategy when choosing a follow-up plan. Third, the single-center design of the study will only allow us to conclude on our practice, and it will be difficult to extrapolate our results except among teams with the same practices as us. Fourth, it might also be interesting to analyze a potential economic impact with the consumption of several medication, analgesics and an increase in the hospital staying, specifically in case of consecutives methods. These secondary analyses were not originally planned, but should be done using registered data.

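### Continuous outcomes measured under three ripening methods are assigned only two-group tests, and the plan does not say how women who switch method are grouped

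*Protocol article*

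**What the plan says.** Three methods are studied. The Target population section states: "The choice of the method of cervical ripening (DBC, vaginal dinoprostone insert or oral misoprostol) is left to the free discretion of the obstetrician", meaning the "obstetrician responsible for the woman at the beginning of IOL".

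Under Trial design and follow-up, if labor has not begun or the cervix is still unfavorable after 24 hours, "repeating the vaginal dinoprostone insert or oral misoprostol or switching to another method are options to the free discretion of the treating physician". Ripening before oxytocin may last "with a maximum of 3 days in our obstetric team". The Discussion expects sequences of methods: it raises a possible cost analysis, "specifically in case of consecutives methods".

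The Statistical analysis section gives the comparison in general terms: "Maternal and perinatal outcomes will be compared according to cervical ripening method". Continuous data are to be "compared by t tests (or Mann-Whitney tests when appropriate". For the rest, "categorical data will be described by percentages and compared by" chi-square or Fisher's exact tests. EQ-5D scores are compared by mean differences with 99% intervals. The significance threshold is 0.05. No multiplicity rule and no particular pair of methods is named.

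**The concern.** Two things do not fit a three-method study in which the method can change.

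- **Test.** A t test or a Mann-Whitney test compares two groups. With three methods, the rule as written can be carried out only by choosing one pair, pooling two methods, or testing all three pairs. The first two leave room to choose after seeing the data. The third raises the error rate if each pair is tested at 0.05.
- **Group.** A woman who starts with the balloon and then receives dinoprostone has no stated place in a comparison by ripening method. The choice matters because a second method is given only when the first has not worked by 24 hours. Any grouping that moves switchers elsewhere removes failures from the group they started in. The removal may be unequal: the repeat options listed are for dinoprostone and misoprostol, not the balloon. Among those options, a balloon non-responder continues ripening only by switching, while a prostaglandin non-responder may repeat and stay in a single-method group.

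The second issue reaches vaginal delivery, which is part of the primary endpoint.

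**Working it through.** **The plan's own figure.** The article gives no error rate and no power calculation. Its one figure is recruitment of 800, used below as the total. From Sample size estimation: 2,600 × 0.20 / 12 = 43.3 per month, and 43.3 × 20 × 0.95 = 823. With the rounded 40 per month, 40 × 20 = 800. The figure reproduces.

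**Which outcomes the two-group rule touches**

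| Outcome | Test or summary named | Fits three groups? |
|---|---|---|
| Vaginal delivery, binary morbidity, dissatisfaction (score below 5), EQ-5D domains dichotomised | Chi-square or Fisher | Yes |
| EQ-5D score | Mean differences, 99% intervals | Pairwise, but strict |
| Pain at insertion and in situ | t or Mann-Whitney | Asked only of balloon and dinoprostone women, so two groups |
| Blood loss, cord pH, base excess, oxytocin quantity; duration and satisfaction scores if analysed as scores | t or Mann-Whitney | No |

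**Error rate for the last row.** Three pairwise tests at 0.05, no true differences:

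- If the tests were independent: 1 − 0.95³ = 0.143.
- Each pair shares a group with another, so the true figure is lower. Simulation with 800 women and 10,000 replicates per split gave:

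| Split (assumed) | Any of three pairwise tests | One-way ANOVA |
|---|---|---|
| 267/267/266 | 0.120 | 0.051 |
| 400/240/160 | 0.116 | 0.045 |
| 500/200/100 | 0.125 | 0.054 |

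That is about 12% per outcome, against about 5% for one three-group test. For EQ-5D scores judged by 99% intervals, the family-wise rate is at most 3 × 0.01 = 3%.

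**Grouping of switchers (illustration, all rates assumed).** The documents give no switching frequency. Suppose the methods are equally effective and a fraction *f* are not ripe at 24 hours. Vaginal delivery is *p*₁ if ripe and *p*₂ if not. All balloon non-responders switch. Among prostaglandin non-responders a fraction *s* switch and the rest repeat.

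- By first method, every group has (1 − f)p₁ + f·p₂, so the difference is 0.
- By methods received, balloon-only = p₁.
- By methods received, prostaglandin-only = [(1 − f)p₁ + f(1 − s)p₂] / [(1 − f) + f(1 − s)].

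Ranges tried: f from 0.2 to 0.4, s from 0.3 to 0.7, (p₁, p₂) = (0.85, 0.60) or (0.80, 0.65).

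- Smallest (f = 0.2, s = 0.7, 0.80/0.65): (0.640 + 0.039) / 0.86 = 0.790 against 0.800, a spurious 1.0 point. By first method, all groups are 0.770.
- Largest (f = 0.4, s = 0.3, 0.85/0.60): (0.510 + 0.168) / 0.88 = 0.770 against 0.850, a spurious 8.0 points. By first method, all groups are 0.750.
- Balloon-only against a several-methods group: p₁ − p₂, which is 15 to 25 points.

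The assumption that every balloon non-responder switches drives the 1 to 8 points. If some went to oxytocin without a second method, they would stay in the balloon-only group and the difference would shrink. If switching were equally common after every method, it would be zero between single-method groups.

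**The case against.** A reader might infer that the planned tests are wrong throughout, that the method groups overlap, and that the comparison is biased. The documents support none of these as stated.

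- Chi-square and Fisher's exact tests take three groups, so vaginal delivery and the other binary outcomes already have a valid overall test. The 12% cannot be applied to them.
- The t-test sentence is general. It also serves two-level contrasts, such as satisfied against dissatisfied women, and the device pain scores.
- Nothing says that women are classified by methods received. The method is described as chosen at the beginning of induction, which points towards the first method. A full protocol or analysis plan may settle it, and neither is shown.
- The size of any switching bias rests on invented rates, and its direction is not general. It depends on how far outcomes of switchers and non-switchers differ within each method. Repeating the same method removes no one from a group.

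All of this stands and limits the point. It does not remove it. For continuous outcomes under three methods, the article commits to tests that do not fit, which is a stated choice rather than an omitted detail. On grouping, the description of when the first choice is made is not carried into the analysis text. The Discussion acknowledges selection bias from free choice of the first method, but not the effect of later switching.

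**Conclusion.** The point holds in limited form.

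1. For continuous outcomes measured under all three methods, only two-group tests are named. Run pairwise at 0.05 without adjustment, they give about a 12% chance of at least one false positive per outcome. This assumes that all three pairs are tested and that no multiplicity rule exists elsewhere.
2. The comparison group is not defined although switching is allowed. The resulting bias is conditional: roughly 1 to 8 points between single-method groups under the assumed rates if women are grouped by methods received, and zero under the same rates if grouped by first method. The documents do not show that the biased grouping is intended.

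Both are worth correcting before analysis, because the study means to guide the choice of method. Neither invalidates the design.

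**What to change.** - For continuous outcomes under three methods, name ANOVA or Kruskal-Wallis, or a 2-degree-of-freedom test of method in a regression. Make pairwise contrasts at 0.05 only if the overall test is significant. With three groups this holds the family-wise rate at 5%: if all three are equal the overall test protects, and if one differs only one true null pair remains.
- State that the main comparison classifies each woman by the first method started, whatever follows. Report need for a second method as an outcome, and show sequences of methods descriptively.

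The cost is analysis wording and a little extra work. Some pairwise P values below 0.05 will no longer be claimed when the overall test is not significant. Method is listed among the data collected, but the article does not say that first and later methods are recorded separately, so this should be confirmed in the database. Grouping by first method does not remove confounding from the obstetrician's choice.

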**Methods and design:**

The MATUCOL study is a monocentric, prospective, observational study of all consecutive women who required cervical ripening (Bishop score <6) using different methods (DBC, vaginal dinoprostone, oral misoprostol) with a live fetus at term (≥37 weeks) between January 2020 and August 2021. The outcomes will be mode of delivery, maternal and neonatal morbidity, discomfort/pain assessments during cervical ripening, women’s experience and satisfaction, and the impact of cervical ripening on the health-related quality of life at 3 months. If it reports a significant efficacy/safety/perinatal morbidity/women’s satisfaction/quality of life at 3 months post-delivery associated with a method of cervical ripening in a specific situation (gestational and/or fetal disease) using a multivariate analysis, its use should be reconsidered in clinical practice.

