Naturally, each of the different mechanical or pharmacological induction method has a different mechanism of action, as well as safety and adverse-effect profile. Although data comparing different methods for IOL are available [2–5], there are insufficient comparative data to determine which of the methods is the most effective and safety profile with the best women’s experience and overall satisfaction at immediate and long-term. Variation in indications for IOL, parity, and gestational age at induction, as well as other demographic features, undoubtedly also affects clinical results. Variations in clinical practice, especially in case of consecutives methods, may also lead to an important delay between the onset of cervical ripening and the onset of the labor that can depreciate women’s well-being and satisfaction and induce morbidity. In order to try to tease out the nuances in safety and efficacy outcomes, large prospective observational studies are needed to assess whether methods is associated with more vaginal delivery, good women’s experience and good short- and long-term quality of life (QOL) at 3 months post-delivery in various maternal (obesity, previous diabetes, previous cesareans scar.) and obstetric (breech presentation, twins…) conditions, and for different indication for IOL (gestational diabetes mellitus, prolonged pregnancy, prelabor rupture of the membranes, pregnancy-associated hypertensive disorders, fetal growth restriction…). We are constantly looking for the optimal protocol of IOL for each woman before the widespread use of a specific device for a specific maternal or obstetric condition or IOL indication.

The present study aims to elucidate whether cervical ripening method is associated with increase rate of vaginal delivery, good women’s experience and unaltered long-term quality of life after cervical ripening at term regarding maternal and obstetric characteristics.

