## Endpoints

The primary endpoint in this study is the effectiveness (vaginal delivery), the safety (maternal and neonatal morbidity), and the women’s experience and overall satisfaction in immediate postpartum period regarding cervical ripening methods, maternal and obstetric conditions. The secondary endpoint is the impact of cervical ripening on the health-related QOL at 3 months according to the methods.

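### The abstract promises a multivariate analysis of efficacy, safety and perinatal morbidity by method, but the Statistical analysis section gives vaginal delivery and morbidity only unadjusted comparisons, which are open to confounding by indication

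*Protocol article*

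**What the plan says.** **Endpoints.** The section begins "The primary endpoint in this study is the effectiveness (vaginal delivery), the safety (maternal and neonatal morbidity" and then adds women's experience and satisfaction. Vaginal delivery and morbidity are thus part of the primary endpoint. Quality of life at 3 months is secondary.

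**Allocation.** Under Trial design and follow-up, the choice of method "is left to the free discretion of the obstetrician responsible for the woman at the beginning of IOL". The same sentence then sets a limit on that discretion: "but in accordance with the institutional local guidelines for cervical ripening". The content of those guidelines is not given.

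**Statistical analysis.** Continuous data are compared by t or Mann-Whitney tests; "categorical data will be described by percentages and compared by" chi-square or Fisher tests. Then: "Maternal and perinatal outcomes will be compared according to cervical ripening method". One multivariable model is named, a logistic regression, and its outcomes are dissatisfaction in the immediate postpartum period and poor quality of life at 3 months.

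**Abstract, Methods and design.** The abstract describes the case where a significant result on efficacy, safety, perinatal morbidity, satisfaction or quality of life is "associated with a method of cervical ripening in a specific situation (gestational and/or fetal disease) using a multivariate analysis, its use should be reconsidered".

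**Prognosis and bias.** The Rational subsection of the Introduction states: "Variation in indications for IOL, parity, and gestational age at induction, as well as other demographic features, undoubtedly also affects clinical results". The limitations in the Discussion say of the discretionary choice: "That can introduce selection bias if participants regarding cervical ripening methods differ in important ways other than outcome". No analytic remedy is offered there.

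**The concern.** The abstract and the statistical section give different accounts of how two of the three parts of the primary endpoint will be analysed. The abstract has efficacy, safety and perinatal morbidity examined in a multivariate analysis. The statistical section gives them crude tests and keeps the model for dissatisfaction and quality of life. The secondary endpoint is thus assigned an adjusted model while vaginal delivery is not.

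The study is not randomised, and the document itself says that indication, parity and gestational age influence results. If obstetricians tend to use one method more in women with a less favourable outlook, a crude comparison credits or blames the method for that difference. An analyst who followed the statistical section literally would report such a comparison as the main result, in a study meant to inform which method suits which woman.

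**Working it through.** **1. The passages side by side**

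| Outcome | Endpoint status | Abstract | Statistical analysis section |
|---|---|---|---|
| Vaginal delivery | Primary | Multivariate | Crude tests by method |
| Maternal and neonatal morbidity | Primary | Multivariate | Crude tests by method |
| Experience and satisfaction | Primary | Multivariate | Logistic model (for dissatisfaction) |
| Quality of life at 3 months | Secondary | Multivariate | Logistic model (for poor quality of life) |

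The first two rows disagree; the last two do not. The Discussion also says that factors associated with efficacy and safety will be identified, and that methods will be analysed within particular indications or groups of women. It names no model for this, and restricting to one indication does not remove confounding among the women within it.

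**2. The plan's own figure**

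The only relevant number is the recruitment target of 800.
- 40 per month × 20 months = 800.
- Unrounded: 2,600 × 0.20 / 12 = 43.3 per month; 43.3 × 20 × 0.95 = 823, within 3% of 800.

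This is a feasibility count. The document states no outcome rates, no split between methods and no case mix by method, so the size of any confounding cannot be derived from it.

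**3. Illustration on assumed inputs**

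Assumed: vaginal delivery 70% in nulliparous and 92% in parous women; no true difference between methods; three equal groups, 800 / 3 ≈ 267 women per method; two-sided 5% test of two methods. Only the total of 800 comes from the document.

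Crude rate for a method = (nulliparous share × 0.70) + (parous share × 0.92).

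*Nulliparous share 70% vs 50% (20 points apart):*
- 0.70 × 0.70 + 0.30 × 0.92 = 0.766
- 0.50 × 0.70 + 0.50 × 0.92 = 0.810
- False difference: 4.4 points
- Standard error: √[(0.766 × 0.234 + 0.810 × 0.190) / 267] = 0.0353
- 0.044 / 0.0353 = 1.25; chance of significance = P(Z > 1.96 − 1.25) ≈ 24%

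*Nulliparous share 75% vs 45% (30 points apart):*
- 0.75 × 0.70 + 0.25 × 0.92 = 0.755
- 0.45 × 0.70 + 0.55 × 0.92 = 0.821
- False difference: 6.6 points
- Standard error: √[(0.755 × 0.245 + 0.821 × 0.179) / 267] = 0.0353
- 0.066 / 0.0353 = 1.87; chance of significance = P(Z > 1.96 − 1.87) ≈ 46%

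With 400 women per method the two figures become 33% and 63%, so a larger sample makes the false result more likely.

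**4. Sensitivity to the assumptions**

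One binary prognostic factor, no method effect, 267 or 400 women per method:

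| Vaginal delivery in the two strata | Share with the factor, by method | False difference | Significant in |
|---|---|---|---|
| 70% / 85% | 55% vs 45% | 1.5 points | 6–7% |
| 70% / 85% | 60% vs 40% | 3 points | 13–17% |
| 70% / 85% | 70% vs 30% | 6 points | 38–53% |
| 60% / 90% | 60% vs 40% | 6 points | 36–50% |
| 60% / 90% | 70% vs 30% | 12 points | 90–98% |

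The range runs from almost no harm to near-certain error. Adjustment for a fully measured factor would return each row to about 5%.

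**5. Is adjustment feasible?**

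At assumed caesarean rates of 15% to 30%, 800 women give 120 to 240 caesareans. At 10 events per parameter that supports about 12 to 24 parameters, enough for the main pre-ripening covariates. Rare morbidity events would support fewer.

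**The case against.** The strongest reply is that the document does foresee adjustment. The abstract names a multivariate analysis for efficacy, safety and perinatal morbidity, and makes reconsideration of a method depend on that analysis and not on a crude test. The Discussion plans to look for factors associated with efficacy and safety. This is also a condensed article, and covariate lists and model details are commonly left to a fuller document. The selection bias is disclosed, and every rate and imbalance in the illustration is assumed.

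Much of this stands, and it rules out several stronger readings that a reader might infer:

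- **That no adjusted analysis is planned anywhere.** This is true of the statistical section for these outcomes, but not of the abstract.
- **That a crude significant result is what would change practice.** The abstract ties that step to the multivariate analysis.
- **That method is assigned by patient profile and the result will be confounded.** The text says discretion within local guidelines, and that bias can arise. Confounding is plausible, but neither its presence nor its size is established.
- **That parity is not collected.** The list of maternal history items is open-ended, so its silence on parity proves nothing.

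The mismatch itself remains. The statistical section does more than omit detail: it says which outcomes receive a model, and vaginal delivery and morbidity are not among them. Disclosing selection bias as a limitation does not supply an analysis that reduces it.

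**Conclusion.** The point holds as an inconsistency with a consequence. The analysis promised in the abstract for efficacy, safety and perinatal morbidity does not appear in the Statistical analysis section, which leaves two parts of the primary endpoint with unadjusted comparisons between methods chosen by clinicians. Followed as written, that section gives a primary comparison open to confounding by indication.

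The size is unknown. The figures of 4.4 to 6.6 points and 24% to 46% rest on assumed delivery rates, assumed parity imbalances and an equal split between methods. With a mild imbalance the effect is negligible (1.5 points, 6–7%). The figures show that the choice of analysis could matter at this sample size, not that the study's result will be wrong.

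**What to change.** In the Statistical analysis section, extend the multivariable model to vaginal delivery and to maternal and neonatal morbidity, and state that it is the main comparison between methods. This brings the section into line with the abstract.

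- Adjust only for variables fixed before ripening starts: for example parity, previous caesarean, age, BMI, Bishop score before ripening, gestational age, indication and fetal presentation. Name parity explicitly among the variables collected.
- For rare morbidity events, use fewer covariates or a propensity score.
- Label the t, Mann-Whitney, chi-square and Fisher comparisons by method as descriptive.

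The cost is a change of wording, a little more analysis work and somewhat wider intervals. The other covariates listed are already among the data described under Trial design and follow-up. Adjustment will not deal with unmeasured reasons for choosing a method, so the selection-bias limitation should stay in the Discussion.

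### EQ-5D mean differences are to be reported with 99% intervals although the only significance rule is P<0.05, and no reason is given for the different level

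*Protocol article*

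**What the plan says.** The Endpoints section of the protocol article makes quality of life the secondary endpoint: "The secondary endpoint is the impact of cervical ripening on the health-related QOL at 3 months according to the methods".

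The Statistical analysis section then says how the EQ-5D-5L scores will be handled. They will be summarised by group as mean and standard deviation and "compared between groups using mean differences (99% confidence index"). The word index presumably stands for interval.

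Two general sentences in the same paragraph also apply to these scores. On the tests: "Continuous data will be described by their means ± standard deviations and compared by t tests (or Mann-Whitney tests when appropriate"). On the threshold: "P values <0.05 were considered to be statistically significant". The threshold sentence makes no exception for quality of life.

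The paragraph gives no multiplicity adjustment and no separate threshold for EQ-5D. It does not say that the 99% interval is descriptive only, and no other outcome is given an interval level.

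**The concern.** A two-sided 99% interval corresponds to a 1% test, while the stated rule is a 5% test. A reader who sees a mean difference with its interval will usually check whether the interval contains zero. For a result with P between 0.01 and 0.05, that check says no significant difference, while the plan's own rule says there is one.

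The score comparison is the main summary of the only named secondary endpoint. The Abstract (Methods and design) also says that a significant association of a method with outcomes that include quality of life should lead to its use being reconsidered. That sentence refers to the multivariable analysis, not to the crude mean difference. It still shows that the word significant carries weight in this study and should have one meaning throughout.

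**Working it through.** **The plan's own figures.** The two figures at issue are the 99% level and the 0.05 threshold, both in the Statistical analysis section. The only numerical target is the 800 women in the Sample size estimation section. It reproduces: 40 per month × 20 months = 800. Without rounding, 2,600 × 0.20 / 12 × 0.95 × 20 = 823, within 3% of the target. No power, effect size or standard deviation is given, and the point does not depend on the 800.

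**Assumptions.** Tests are two-sided (the plan does not state sidedness), the normal approximation holds, and the interval and the P value come from the same test.

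**Step 1: critical values.**
- P<0.05 requires |difference|/SE > 1.960.
- A 99% interval excludes zero only if |difference|/SE > 2.576, that is P<0.01.
- Ratio of widths: 2.576 / 1.960 = 1.31.

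The two readings disagree exactly when |difference|/SE lies between 1.960 and 2.576.

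**Step 2: how often that happens in one comparison.** Let δ be the true difference divided by its SE. The probability of exceeding a critical value c is Φ(δ − c) + Φ(−δ − c). The probability of disagreement is this quantity at c = 1.960 minus the same quantity at c = 2.576.

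| δ | Power at 5% | Power at 1% | Disagreement |
|---|---|---|---|
| 0 | 0.050 | 0.010 | 0.040 |
| 1 | 0.170 | 0.058 | 0.112 |
| 2.27 | 0.622 | 0.380 | 0.242 |
| 2.8 | 0.800 | 0.589 | 0.211 |
| 3.24 | 0.900 | 0.747 | 0.153 |

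The maximum lies near the midpoint of the two critical values, (1.960 + 2.576)/2 = 2.27. The 21% figure belongs to δ = 2.8, where power at 5% is 80%. None of these values depends on group sizes or on the standard deviation.

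**Step 3: what the zone looks like on the scale of the data (illustration only).** The plan gives no group sizes, because the method is chosen by the obstetrician: "The choice of the method of cervical ripening (DBC, vaginal dinoprostone insert or oral misoprostol) is left to the free discretion of the obstetrician". The Sample size section expects to "recruit 800 women, if we assume a participation rate of at least 95% and a 40% drop-out rate at 3 months". Read as 800 women already allowing for participation, this leaves 800 × 0.60 = 480 responders. Two assumed splits:
- Three groups of 160: SE = √(2/160) = 0.112 SD. The zone is 1.960 × 0.112 = 0.219 SD to 2.576 × 0.112 = 0.288 SD.
- Two groups of 240: SE = √(2/240) = 0.0913 SD. The zone is 0.179 SD to 0.235 SD.

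Unequal groups with the same total would move the zone to larger differences.

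**Step 4: after the change.** With a 95% interval, both statements use 1.960 and always agree when they come from the same test. With a 99% interval, they agree only if the EQ-5D threshold is P<0.01.

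**The case against.** The strongest reply is that the plan contains no contradiction. It has one explicit decision rule, P<0.05. The 99% figure is attached only to the presentation of the mean differences, and nowhere does the plan say that an EQ-5D difference will be judged by whether that interval excludes zero. This is correct. A reader might infer that no rule says which level decides, and that the conclusion on the secondary endpoint could therefore be picked after seeing the data. The text does not support that. As written, a result with P between 0.01 and 0.05 is significant, and judging by the interval would depart from the stated criterion.

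A second reply is that a wider interval may be a deliberate precaution, since three methods give three pairwise comparisons. That is possible. Three comparisons at 1% carry a combined error of at most 3 × 0.01 = 0.03, against at most 3 × 0.05 = 0.15 at 5%. But the plan does not give this reason, and applying P<0.05 to the same differences would undo the protection.

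A third reply is that 21% is close to the worst case and that the protocol states no power. This also stands. The figure has to be read per comparison, not per study, and within the range from 4% to about 24%.

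What remains is an unexplained mismatch between two levels that the plan itself fixes. It is not a detail left to a fuller document.

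**Conclusion.** The point holds as a limited inconsistency. The interval level for the EQ-5D mean differences (99%) does not match the only significance rule (P<0.05), and nothing in the protocol article reconciles them. A difference with P between 0.01 and 0.05 would be declared significant beside an interval that includes zero. Under a two-sided normal approximation this happens in 4% of comparisons when there is no true difference, and in at most about 24%.

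The documents do not show whether 99% is a slip for 95% or an intended safeguard. The consequence is unclear reporting of one secondary endpoint in an observational study. The point estimate, the data collected, the primary endpoint and the recruitment target are not affected.

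**What to change.** Report 95% intervals for the EQ-5D mean differences, so that they match P<0.05, and correct index to interval. The P value should come from the same comparison of means as the interval. A Mann-Whitney P value beside an interval for a mean difference can disagree with it at any level.

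If 99% was chosen to guard against multiple comparisons, keep it, state that reason, and set P<0.01 as the threshold for the EQ-5D comparisons. If the 99% interval is meant as description only, a clause saying so is the least that is needed.

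The change costs one sentence and needs no new data or recalculation of the target. It should be made before the 3-month quality-of-life data are analysed.
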